## Abstract

**Background:**

Unemployment rates are higher among people with mental health issues/illness (MHI) than in the general working population, and many of them face the dilemma of whether or not to disclose their MHI when searching for employment. Disclosure can lead to rejection and discrimination, but alternatively can also have important advantages that may be necessary to retain employment. Whether disclosure decisions lead to sustainable employment depends on many factors, of which unemployed people themselves can only influence their decision to disclose or not and the way in which they communicate. This study evaluates the cost-effectiveness of an intervention to support unemployed people with MHI in their disclosure decision and communication.

**Methods:**

This is a two-armed, clustered, randomized controlled trial with longitudinal design and randomization at organization level. An intervention will be examined, which consists of a disclosure decision aid tool (CORAL.NL) for unemployed people and workplace stigma-awareness training especially designed for employment specialists, which focusses on how to support unemployed people in their disclosure decisions. Participants in the intervention group are unemployed people who receive support from trained employment specialists from organizations allocated to the intervention group, and receive the CORAL.NL decision aid after baseline. The control group consists of unemployed people who receive support as usual from employment specialists from different organizations allocated to the control group. Primary outcomes are: cost-effectiveness of the intervention, e.g. healthcare costs, having employment, days until start of employment, independency of social security, having other forms of employment and decision making about disclosing MHI. Secondary outcomes are mental health and wellbeing, stigma and discrimination and work-related factors. Financial income data are collected via the registration systems of Dutch municipalities and Statistics Netherlands, and by questionnaires at baseline, and at 3, 6 and 12 months.

**Discussion:**

If using a decision aid to decide about disclosure of MHI leads to people finding and retaining employment more often, this study will contribute to lowering healthcare and societal costs.

**Trial registration:**

Netherlands Trial Register: NL7798. Registered on 4 June 2019.

## Introduction

People with mental health issues/illness (MHI) are more often unemployed than people without MHI [1–4]. In addition, people with MHI who are employed have higher risk of losing their employment [3, 5] and increased risk of dropping out of work, due to unemployment, work disability, long-term absenteeism or early retirement [6]. Studies have shown that unemployment exacerbates MHI [7] and that when people with MHI start working again, this positively affects their mental health [8].

One of the barriers to people with MHI finding and retaining employment is a negative attitude towards MHI. Multiple studies have shown that the stigma attached to MHI is a risk for not entering the job market or not returning to existing employment [9, 10]. There are several reasons why stigma is a problem for employment, e.g. many employers have negative attitudes towards people with MHI [11–13], which often has negative effects for people with MHI in job applications, contract extensions, job promotions and other career opportunities. Moreover, anticipated discrimination (e.g. avoiding situations or activities because of the fear of being discriminated) and self-stigma (e.g. having negative ideas about oneself because of the MHI) can lead to feeling one is not performing well and therefore had better not try anything [14]. This “why try-effect” discourages people from engaging in relevant activities, such as applying for jobs [15]. International studies have shown that large numbers of people (39-64%) with depression, addiction problems or schizophrenia refrain from applying for jobs or receiving training or education because of possible reactions of others [9, 15, 16]. Furthermore, employees with MHI often do not feel comfortable in talking about their MHI. As a result, employers and employees miss out on the opportunity to talk about the need for support and (temporary) work adjustments. This is unfavorable, because work accommodations, such as adjustment of working hours, can prevent and reduce absenteeism [17].

As a result of stigma, whether or not to disclose MHI in the workplace is a major dilemma for many people with MHI of working age. Disclosure can lead to better work outcomes (i.e. due to appropriate work adjustments), but also to not being hired [18]. The decision whether or not to disclose is often perceived as stressful [19, 20] in which advantages and disadvantages are weighed against each other. In 2010, the Conceal or reveal (CORAL) decision aid was developed by researchers at the Institute of Psychiatry at King’s College London [21]. The purpose of this decision aid is to support decision making about disclosure in the work context [22]. The principle of this decision aid is that people know their own situation best and therefore can make the best choices themselves, but still benefit from help with making a choice. In several follow-up studies [23, 24], using the decision aid was found to be promising: people who used CORAL had less decision-making stress and were significantly more often working full time after 3 months than people who did not use the decision aid [24]. Recently, a randomized controlled trial (RCT) was conducted using a web-based decision aid tool (READY) to help facilitate people in current employment in making disclosure decisions about mental health conditions [25]. Participants who used READY had significantly less decisional conflict about disclosure of a mental health condition and were at a later stage of decision making. These results are very promising for disclosure decisions in the employment setting and would potentially be relevant to implementing and evaluating a similar decision aid tool for unemployed people with MHI in a different context in the Netherlands.

### Objective and research questions

An RCT is conducted to examine the effects of an innovative intervention based on the English CORAL decision aid [23], which has been adapted to the Dutch context and embedded in an intervention for unemployed people with MHI and workplace stigma-awareness training especially designed for employment specialists. Furthermore, factors that facilitate finding employment and factors that hamper this will be studied. The primary research questions of this study are:
Does the intervention more often lead to finding and retaining paid employment for unemployed people with mental health problems, compared to usual guidance in municipal practice, controlled for other factors (e.g. mental health and stigma and discrimination)?Is the intervention cost-effective from a societal perspective (including reintegration costs and healthcare costs)?For whom, under which circumstances and in what way does the intervention work best or less well, and why?

## Methods

The Consolidated Standards of Reporting Trials (CONSORT) 2010 statement and Standard Protocol Items: Recommendation for Interventional Trials (SPIRIT) 2013 statement were followed in the design of the study [26, 27]. The study is funded by The Netherlands Organization for Health Research and Development (project code 535001003). The Ethic Review Board of Tilburg University approved the study design, protocol, information letter, informed consent form and the questionnaires (EC-2018.06 t). The study is registered under trial registration number NL7798.

### Study design

The DECIDES study is a longitudinal, two-armed, clustered RCT of unemployed people with MHI who receive social benefits and/or reintegration support from Dutch municipalities. In this RCT the effects of an intervention that consists of a decision aid for unemployed people (CORAL.NL) and training for employment specialists who guide them in their job-seeking process are evaluated. Randomization took place at organization level (see Fig. 1). Participants are assessed at baseline (T0), and at 3 months (T1), 6 months (T2) and 12 months (T3). In addition, data on employment history (e.g. having employment, income, working hours per week and employment characteristics such as contract and employment type) and social benefits (e.g. having social benefits, duration of social benefits and the amount of social benefits) are extracted anonymously from the registration systems of the municipalities and Statistics Netherlands from T0 to T3 in participants who give consent for this. Collecting data from registration systems is more reliable and is less burdensome for participants. Participation in the study is voluntary and all participants sign an informed consent form for participation, and provide separate consent for the retrieval of their personal data from Statistics Netherlands. Measurements take place in one-by-one appointments with a researcher on the project. Participants can fill out the questionnaire digitally or by paper and pencil. If necessary, the researcher gives support by filling out the questionnaire, e.g. by explaining or reading out loud the questions for illiterate participants. Participants were stimulated to complete follow up by handing out a financial remuneration of 10 euros and by asking several contact options (mobile phone, email) to maintain contact during the participation period. If participants give consent to collect their data from Statistics Netherlands these data will also be collected if they discontinue filling out the questionnaires.

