### Procedure

#### Randomization of employment specialists (ES)

All 72 participating employment specialists were recruited between November 2017 and March 2018 from eight participating organizations. Two researchers presented the study during meetings at the local organizations, provided written information about the study and provided a registration form and informed consent form. After including all employment specialists, the organizations were randomly allocated to either the intervention or control condition, using SPSS software. Cluster randomization was chosen, as individual randomization would have higher risk of contamination between the intervention and control group, because employment specialists within organizations work together on a daily basis. Due to the nature of the intervention, neither the employment specialists nor the researchers can be masked to the allocation to the conditions.

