#### Recruitment of participants

Participants are recruited via the employment specialists working at eight different organizations, and via newspapers and personal letters from the organizations. Inclusion criteria for the study are (1) being unemployed, (2) having sought any treatment (currently or in the past) for MHI, including addiction, by a health professional (e.g. general practitioner (GP), psychologist) and (3) adequate command of the Dutch language, as the intervention and questionnaires are in Dutch. Employment specialists are asked to provide people who meet the inclusion criteria with information about the research and to ask if they are willing to receive more information about the research. If participants give permission to share their contact details with the researchers, they are informed about the research by telephone and the inclusion criteria are checked.

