#### Primary outcomes

The primary outcomes of this study are (1) cost-effectiveness, which will be measured from a societal perspective comparing the intervention with usual care. Healthcare utilization and loss of production will be measured using the Treatment Inventory Costs in Psychiatric Patients (TiC-P), which is a reliable instrument with satisfactory validation [32]. The primary cost-effectiveness outcomes are having employment (yes/no), days from baseline until start employment, receiving social benefits (yes/no) and/or having other forms of employment (i.e. voluntary work, internship). The secondary cost-effectiveness outcome is the EuroQol-5D-5 L, which measures health-related quality of life [33], and (2) decision making about disclosing MHI, measured using the Decisional Conflict Scale, which has adequate test-retest reliability [34], and stage of decision making [35].

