### Sample size

The power calculation is based on data from a recent international study on individual placement and support, which is an evidence-based reintegration model that is also used for people with MHI who want to have regular employment [45] and has the same primary outcome measure, i.e. obtaining employment. In this study, the average percentage employment was 50% in the intervention group and 20% in the control group [45]. Considering 50% and 20% as possible percentages, 36 unemployed people are needed in each group to find a statistically significant difference (with a 5% significance level and power of 80%): 47 participants per group would be needed for power of 90%. However, in this study any cluster effects and the expected dropout of participants over the four measurements must be considered. Considering a dropout rate of approximately 40% because of the vulnerable population, a safe assumption is to have 75 participants per group, which means a total of 150 participants.

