## Trial status

The study is registered under trial registration number NL7798 (registered 4 June 2019 - retrospectively registered; https://www.trialregister.nl/trial/7798). Participant recruitment started in April 2018 and ended in July 2019. Data collection will end in July 2020. The data gathering is in progress. According to the municipalities, there were difficulties in engaging and scheduling appointments with the target group, which delayed the submission of the study protocol paper. Priority was given to the hundreds of face-to-face meetings that need to be scheduled for data gathering. However, the researchers have no access to the primary outcome measures of the study until 3 months after the final measurement, as the primary outcome data will be retrieved from a different organization (i.e. Statistics Netherlands, an organization with very strict data security) 3 months after the end of the data gathering process.

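### Researchers who know the allocation may, where help is needed, explain items of the self-reported disclosure-decision primary outcomes, so the help given could differ by arm

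*Protocol article*

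**What the plan says.** Under Study design, the article sets out how data are obtained: "Measurements take place in one-by-one appointments with a researcher on the project". Participants normally complete the questionnaire themselves, on screen or on paper. Help is conditional on need, and in that case "the researcher gives support by filling out the questionnaire, e.g. by explaining or reading out loud the questions for illiterate participants". Illiterate participants are given as an example, not as the only case.

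Under Randomization of employment specialists, the article states that "neither the employment specialists nor the researchers can be masked to the allocation to the conditions".

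Under Primary outcomes, the second primary outcome is "decision making about disclosing MHI, measured using the Decisional Conflict Scale", together with stage of decision making. Table 1 schedules both at T0, T1, T2 and T3.

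Under Trial status, the article says that researchers have no access to the primary outcome measures until three months after the last measurement, because "the primary outcome data will be retrieved from a different organization", namely Statistics Netherlands.

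**The concern.** Explaining an item is different from reading it out. It replaces the fixed wording of the scale with the researcher's own words, and here the researcher knows the arm. The two disclosure-decision instruments are the most sensitive to this. According to the section on CORAL.NL, the aid works through the pros and cons of disclosure, personal needs and values, and a plan. A researcher who clarifies an item about the disclosure decision is speaking on the same subject. The explanation might echo the aid in one arm, or supply some of its content to a control participant.

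Any net difference between arms in how items are explained adds to, or subtracts from, the estimated effect on a primary outcome. Analysis by assigned arm and multiple imputation do not address this kind of error. The safeguard under Trial status does not reach it either. That safeguard concerns access to register data, whereas these two instruments are completed at an appointment with the researcher.

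**Working it through.** **The passages side by side**

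1. Who is present: a project researcher, one to one (Study design).
2. What that person may do: explain or read out questions when needed (Study design).
3. What that person knows: the allocation (Randomization of employment specialists). Organizations were allocated after all employment specialists had been included, which ran to March 2018. Participant recruitment began in April 2018 (Trial status). On that order, the arm was known at T0 as well as at follow-up.
4. What is being answered: among other scales, two self-reported primary instruments at all four time points (Primary outcomes, Table 1).
5. How often help is needed: not stated. Inclusion requires "adequate command of the Dutch language", which limits the need but does not exclude poor reading. The CORAL.NL section reports that some pilot respondents had trouble reading or concentrating.

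**The plan's own sample-size figure**

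The article states: "Considering 50% and 20% as possible percentages, 36 unemployed people are needed in each group". With unpooled variance, a two-sided 5% level (sidedness is not stated) and 80% power, n = (0.25 + 0.16) × (1.96 + 0.84)² / 0.30² ≈ 35.8, so 36 is reproduced. At 90% power the formula gives 47.9, against 47 stated. These figures concern employment and do not bear on this point. What is used below is the planned 75 per arm less about 40% dropout: 75 × 0.6 = 45 per arm.

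**Size of a possible bias (assumed inputs)**

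Let p be the share helped, taken as equal in both arms, and d the net difference between arms in the shift that the help causes. Then bias b = p × d. If explanations shift answers equally in both arms, d = 0 and the bias vanishes. The documents give neither p nor d. As assumptions, p = 20-50% and d = 0.2-0.5 SD:

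- Low end: 0.2 × 0.2 = 0.04 SD.
- High end: 0.5 × 0.5 = 0.25 SD.

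The standard error of the arm difference in SD units, ignoring clustering, is √(2/45) = 0.211. With no true effect, the rejection rate is 1 − Φ(1.96 − b/0.211) + Φ(−1.96 − b/0.211):

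| b (SD) | Rejection rate |
|---|---|
| 0.04 | 5.4% |
| 0.10 | 7.6% |
| 0.175 | 13.2% |
| 0.25 | 22.0% |

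For scale, the difference detectable with 80% power is 2.80 × 0.211 = 0.59 SD.

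The sign of d is unknown. If a bias of the same size works against a true effect of 0.59 SD, power is Φ(2.80 − b/0.211 − 1.96). That is about 74% at b = 0.04 and about 37% at b = 0.25.

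**What baseline can absorb**

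Let b₀ be the bias at T0 and b₁ the bias at follow-up. A comparison of changes from T0 leaves b₁ − b₀. Adjustment for the T0 value leaves b₁ − βb₀, where β is the regression slope of follow-up on baseline. If cueing is constant over time (b₁ = b₀), the first removes it and the second reduces it. Cueing that arises only after T0, once the aid is in use, remains in both.

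**The case against.** The strongest reply is that help is the exception. Self-completion is the default, explanation depends on need, the example is illiteracy, and one of the two forms of help is plain reading aloud, which carries little risk. This stands. A reader might infer that researchers routinely explain the primary scales to everyone at every visit, but the text does not support that.

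A second reply is that the magnitude rests wholly on assumption. This also stands. The 22% needs half of participants helped and a net half-SD arm difference among them at the same time. Even then the bias of 0.25 SD is less than half the 0.59 SD detectable difference.

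Third, a reader might infer that the bias favours the intervention. The documents do not show a direction. Giving controls some of the aid's content through an explanation could shrink the difference instead.

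Fourth, the planned analysis is longitudinal and T0 was also taken by researchers who knew the arm, so a constant effect may be partly absorbed. This stands in part. The article does not say how T0 enters the model, and cueing that starts after T0 is untouched.

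Fifth, a script for explanations may exist in a fuller protocol or field manual. That is possible, and the absence of a script is not the point here. The point is that the stated rule permits explanation by unmasked staff and applies to the questionnaire as a whole, primary scales included.

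Finally, intervention participants know that they used the aid, so self-report may differ by arm anyway. That is true, but the researcher's explanation is a separate source, and one that can be controlled.

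**Conclusion.** The point holds as a modest, avoidable risk to the Decisional Conflict Scale and stage of decision making. The article itself provides for unmasked researchers to explain items of self-reported primary outcomes on the same topic as the intervention. Whether any bias results, how large it is and in which direction it runs cannot be read from the document. The range of 0.04-0.25 SD (rejection in about 5-22% of trials under no effect, 45 per arm, no clustering) depends entirely on the assumed 20-50% helped and 0.2-0.5 SD net shift, and the true figure may be smaller.

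A reader might go further and conclude that the trial's employment findings are compromised. They are not on this ground: employment and benefit data taken from registers are not exposed. Other questionnaire scales, such as the TiC-P and EQ-5D-5L, share the exposure in principle. The statement under Trial status that researchers lack access to the primary outcomes can be true only of the register outcomes.

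**What to change.** For the Decisional Conflict Scale and stage of decision making, at all remaining visits (data collection runs to July 2020):

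- Limit help to reading the item word for word. Where an item is still not understood, use one fixed neutral wording, identical in both arms.
- Record at each visit whether completion was unaided, read aloud or explained. Enter this retrospectively for past visits where it was noted.
- Keep all participants in the primary analysis. Add a sensitivity analysis of these two outcomes without explained questionnaires, and state that it selects on a feature arising after randomization.
- Under Trial status, restrict the statement about no access to primary outcomes to the register outcomes.

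The cost is a written instruction, a short set of fixed wordings, one field on the visit form and one extra analysis. No staff are added. There are two downsides. Some more items may go unanswered among participants with low literacy. Also, recruitment ended in July 2019, so baseline visits cannot be changed and administration will differ between T0 and later visits. That change is the same in both arms.

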**Fig. 1 Fig1:**
[figure not shown]
Flow diagram of the study protocol. MHI, mental health issues/illness

### Setting

In the Netherlands, people older than 18 years are entitled to social benefits if they have insufficient income or capital and are unable to make use of another provision or benefits, such as disability benefits. In order to receive social benefits, (re)integration obligations must be met, such as cooperating in the support that the municipality offers aimed at entering the job market or returning to existing employment. This support is offered per municipality, and is often organized differently per municipality. Regarding disabilities and employment, the Netherlands has confirmed the U.N. Convention on the Rights of Persons with Disabilities [28] and has its own Disability Discrimination Act. The convention and act indicate that organizations and employers need to ensure that employees with disabilities have access to reasonable accommodations at work [29]. This anti-discrimination legislation may influence the employment status of people with disabilities in various ways. Employees do not have legal obligations to inform the employer about a disability as long as the impairment does not result in any endangerments at the workplace. However, disclosure of a health problem may be necessary for access to accommodations whereby this only can be implemented if the employer has knowledge of the disability, especially when natural support in the workplace is not available. Organizations commonly perceive such legislation and policies as a burden, e.g. because Dutch employers must pay at least 70% of the salary of a sick employee during the first 2 years of sickness absence [30]. This in fact might lead employers to try to avoid hiring a person with a disability [29].

